### Randomisation and allocation concealment

Randomisation will be carried out using computer-generated random numbers (http://www.randomization.com). One research assistant will be responsible for generating the random numbers and putting them into sequentially numbered opaque sealed envelopes. This research assistant will not involve in participant recruitment, intervention implementation, outcome assessment, and/or data analysis. The eligible participants will be randomly assigned to either the intervention group (odd numbers) or the control group (even numbers) according to the random numbers.

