## Methods

### Study design

The protocol describes a multicentre, two-arm, assessor-blind randomised controlled trial (RCT), with randomisation of family members of residents with dementia rather than residential care facilities. The CONSORT flow diagram is shown in Fig. 1. Although there might be crossover effects between family members within a residential care facility in which some belong to the intervention group and others to the control group, we still choose an individual RCT design because of its ability to deal with known and unknown confounding factors. To avoid the contamination between participants of the two groups, some strategies will be employed, such as asking participants in the intervention group not to share the intervention information with others.

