### Participants and recruitment

Family members of residents with dementia will be recruited from four to six medium-sized residential care facilities (100–300 beds) in Xi’an, Shaanxi, China. Posters will be available in the studied facilities to encourage more interested and eligible family members to participate in the trial. Potentially eligible and interested participants will be referred to the researchers by nurses who work in the studied facilities. The researchers will then approach the potentially eligible participants to determine their eligibility and invite them to participate in this trial. Information sheets will be provided to the eligible participants and any questions or inquiries will be answered by the researchers.

To be eligible, the participants should (a) be family members of residential care facility resident who has a medical diagnosis of dementia, (b) be aged 18 years or older, (c) provide the most hours to their relative’s care after placement, (d) have a smartphone and be able to use it, (e) be willing to participate in this study, and (f) be able to read, write and understand Chinese. Exclusion criteria of the participants are: (a) having severe mental disorders (e.g. schizophrenia), (b) having impaired cognitive ability, (c) being a family member whose relative with dementia is at end of life (i.e. the life expectancy is projected to be six months or less), (d) being a paid caregiver, (e) receiving psychotherapies during the period of this study, and (f) participating in other relevant psychosocial interventions or programmes during the period of this study. Participant recruitment for this trial is currently ongoing.

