### Sample size estimation

Sample size is estimated based on the primary outcomes, specifically, changes in family members’ stress. In this study, effect size of family members’ stress reduction is anticipated to be medium at 0.50. It is estimated that a sample size of 128 participants (64 per group) will provide this study with 80% power at 5% level of significance (two-tailed). Attrition rates in previous studies ranged from 0% [21] to 34.3% [34], most of which were less than or around 15% [16–18, 20]. In consideration of 15% attrition rate, sample size of this study is finally estimated to be 150 family members (75 per group).

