### Data management and analysis

Data will be double entered and checked in EpiData 3.1 (The EpiData Association, Odense, Denmark) and will then be exported to Statistical Package for the Social Sciences (SPSS) version 25.0 (IBM Corporation, Armonk, New York, USA) for analyses. The distribution normality of the continuous variables will be tested by One-Sample Kolmogorov-Smirnov test. The baseline homogeneity between the intervention group and the control group will be tested using the Student’s T test, Mann-Whitney U test, Chi-square test, and Fisher’s exact test, where appropriate. All outcome measures will be compared within and between groups. The generalised estimating equation (GEE) model will be utilised to analyse the intervention effects, with controlling for confounding factors such as the family members’ age, gender, educational attainment, and relationship with the residents, and the residents’ age, gender, educational attainment, type of dementia, and length of stay in the facility. The analyses will be performed based on the intention-to-treat (ITT) principle. For ITT analysis, missing data will be dealt by using the last observation carried forward method, whereby the last available measurement for each participant at the time point prior to withdrawal from the study is retained in the analysis [47]. Statistical significance will be set at *p* < 0.05; all tests will be two-tailed.

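### Facility is not used in the described allocation or named among the model covariates of a four-to-six-facility trial; name it as a fixed effect in every outcome model.

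*Protocol article*

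**What the plan says.** Under Study design, the protocol article describes a "multicentre, two-arm, assessor-blind randomised controlled trial (RCT), with randomisation of family members of residents with dementia rather than residential care facilities". Under Participants and recruitment, family members are "recruited from four to six medium-sized residential care facilities (100–300 beds) in Xi’an, Shaanxi, China", and recruitment is reported as ongoing.

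Under Randomisation and allocation concealment, "Randomisation will be carried out using computer-generated random numbers", placed in sequentially numbered opaque sealed envelopes. Participants are then "randomly assigned to either the intervention group (odd numbers) or the control group (even numbers) according to the random numbers". The section mentions neither facility nor blocks. It does not say whether the numbers are independent draws or a shuffled list.

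Under Data management and analysis, the GEE model adjusts for nine named covariates. Four describe the family member (age, gender, education, relationship with the resident) and five the resident (age, then "gender, educational attainment, type of dementia, and length of stay in the facility"). The list is introduced as examples. Time spent in the facility is on it; which facility is not.

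**The concern.** In a multicentre trial, site is normally a stratification factor, a model term, or both. Here it is neither in the allocation rule as described nor in the covariate list, although the article gives reasons to expect differences between facilities:

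- The BPSD section has each resident's primary nurse supply the NPI-Q ratings, so differences between raters are tied to facility.
- The Family involvement section sums how often families talk with care workers, nurses, physicians and administrators, which depends on how a facility is staffed and run.
- The Background names facility fees, suboptimal facility care and relations with staff as stressors, and says that fees and care quality may need action by government rather than by this intervention.

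If facilities differ on an outcome, that variation stays in the residual. If the arms are also unevenly spread over facilities, part of it enters the observed difference between arms in that particular trial.

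**Working it through.** **1. The plan's own sample size.** Inputs from Sample size estimation: standardised effect 0.50, two-sided 5%, power 80%, attrition 15%. A two-sample t-test needs 63.77, so 64 per arm, or 128 in total (power 0.801). Inflation gives 128/0.85 = 150.6, against 150 stated. The plan's figure reproduces. With 150 × 0.85 = 127.5 evaluable (63.75 per arm), power is 0.800.

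**2. Imbalance within facilities, independent draws.** Assume equal-sized facilities (size 150/k, rounded down) and Binomial(m, 0.5) within each. Let p be the chance that the smaller arm holds 35% or less of one facility's participants. The chance for at least one of k facilities is 1 − (1 − p)^k.

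| Facilities k | Size m | p, one facility | At least one facility |
|---|---|---|---|
| 4 | 37 | 0.047 | 0.175 |
| 5 | 30 | 0.099 | 0.405 |
| 6 | 25 | 0.108 | 0.495 |

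**3. The same, shuffled list.** If the numbers are a random permutation of 1 to 150, exactly 75 are odd and 75 even, so the arms are equal overall. Simulating that list with the same facility sizes gives a chance of at least one 65:35 or worse split of about 8% (four facilities), 26% (five) and 36% (six). Balance overall does not give balance within facilities.

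**4. Precision.** Let r be the share of outcome variance explained by facility. The article gives no such figure, so r is an assumption. Removing that share leaves a residual SD of √(1 − r), so the effective standardised difference is 0.50/√(1 − r) and the standard error falls by 1 − √(1 − r).

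| r (assumed) | Effective difference | Fall in SE | Power at 127.5 evaluable |
|---|---|---|---|
| 0 | 0.500 | 0 | 0.800 |
| 1% | 0.503 | 0.5% | 0.804 |
| 2% | 0.505 | 1.0% | 0.808 |
| 5% | 0.513 | 2.5% | 0.820 |
| 10% | 0.527 | 5.1% | 0.840 |

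**5. Size of the chance shift.** Under unrestricted allocation, the facility component of the arm difference has SD about √(4r/150) in outcome SD units. At r = 5% this is √(0.20/150) = 0.037. The unadjusted standard error is about √(4/150) = 0.163, and the planned effect is 0.50.

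**The case against.** The strongest reply is that little is lost. Individual randomisation leaves the comparison unbiased on average. The chance shift in step 5 is small beside the planned effect and is already covered by the unadjusted standard error. The 65:35 threshold is arbitrary and does not itself measure harm. All of this stands, and it limits the point to precision and protection against an unlucky allocation.

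It can also be said that the covariate list is illustrative, and that a journal article may leave strata and the final model to fuller documents. That stands in part: facility is unnamed, not excluded. But the article does set out an allocation rule and names nine covariates, several of them less obviously tied to NPI-Q ratings or staff contact than site is. The Background describes high fees and suboptimal care as general problems in China, not as differences among the recruited facilities. The expectation that facilities differ is therefore an inference, strongest for NPI-Q and staff contact and weaker for stress, the outcome used for sizing.

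A reader might go further and infer that the odd/even rule is simple randomisation and so cannot deliver "sample size of this study is finally estimated to be 150 family members (75 per group"). The article does not support that. It does not say whether the list is restricted, and odd/even applied to a shuffled 1 to 150 gives exactly 75 and 75. The figure of 75 is in any case a planning target. If the draws were independent, a 65:85 split would still leave power at 0.793 against 0.800, and the average over all splits would be 0.797: less than one point.

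**Conclusion.** The point holds as a moderate weakness of design and analysis. As described, neither the allocation nor the named covariates use facility, in a trial where some outcomes plausibly depend on it. The randomised comparison is not biased on average.

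A facility split of 65:35 or worse somewhere in the trial has a chance of about 18% to 50% under independent draws and about 8% to 36% under a shuffled list, for four to six equal-sized facilities. The gain from adjustment is 0.4 to 4 points of power if facility explains 1% to 10% of outcome variance. The equal facility sizes and the variance shares are assumptions. The required sample size does not change.

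**What to change.** Name facility as a fixed effect in the GEE model for every outcome, and record this with a date before outcomes are analysed. Facility of recruitment should already be on record, so no new data are needed. This also settles a choice that the open-ended covariate list would otherwise leave until after the data are seen.

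The cost is 3 to 5 parameters for four to six facilities. They come on top of roughly 20 parameters for the nine covariates already named, using the categories under Background characteristics: education 3 + 3, relationship 4, dementia type 5, and five single terms. That is affordable with about 128 evaluable participants, but the total should be looked at as a whole.

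Optionally, envelopes not yet issued could be replaced by facility-stratified permuted blocks of varying size, leaving existing allocations untouched. This needs a short dated amendment and produces a mixed allocation scheme. The analysis change does not depend on it. It would also help to state whether the random-number list is restricted.

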### Blinding

Participants and implementer(s) of the intervention will not be blinded to the participants’ group allocation. Outcome assessors will be blinded to the participants’ group allocation until the entire data analysis has been completed.

### Intervention group

Participants in the intervention group will receive a six-session group-based (6 to 10 participants) online education intervention. The intervention will be delivered on a weekly basis, approximately 60 min per week. Participatory approaches (e.g. experience sharing, brainstorm) will be used during the intervention delivery. Participants will be encouraged to complete the whole intervention through text message reminders; yet the situation that participants discontinue the allocated intervention because their relative with dementia dies or moves out of the studied facilities will be allowed.

Session 1 aims to facilitate the participants to reappraise the situations they are facing with, through improving their understanding of dementia. Specifically, the researcher will provide the participants with basic dementia knowledge especially its progression and manifestations at different stages. These kinds of information are anticipated to reduce the participants’ uncertainty about dementia, which may further facilitate the participants to reappraise the situations they are facing with.

Session 2 aims to help the participants manage negative emotions after residential care placement. Firstly, the participants will be encouraged to share their experiences of managing negative emotions after residential care placement. The researcher will introduce the participants some emotion management strategies (e.g. accepting the reality, benefit finding, and humour). In particular, the researcher will guide the participants to find benefits of residential care placement in order to help them reframe stressful situations by wresting positive values form adversity.

Sessions 3 to 5 aim to improve the participants’ problem-solving skills in controlling or managing the stressful situations during visits. In session 3, the researcher will impart the participants communication tips with people with dementia (e.g. approaching from the front, minimising distraction, asking short and answerable questions). In session 4, the researcher will guide the participants to analyse the causes or underlying meanings of BPSD in people with dementia. Strategies of how to deal with BPSD (e.g. delusion, hallucination, agitated behaviour, wandering, irritability, anxiety, appetite changes, and inappropriate sexual behaviour) during visits will be introduced to the participants. In session 5, the researchers will help the participants to recognise their role changes and potential benefits of family involvement after residential care placement. Key points of establishing harmonious family-staff partnership (e.g. information sharing, setting realistic expectations) will be also introduced to the participants.

Session 6 aims to help the participants identify and call upon social support, which is an important coping resource when encountering stressful situations. The participants will be invited to depict their available social support network and will be encouraged to call upon it when encountering stressful situations. Additionally, approaches to resolving conflicts with other family members (e.g. organising a family conference) will be provided to the participants.

### Control group

Family members allocated to the control group will be allowed to use community-based resources and irregularly chat with the facility staff but will not be provided with additional interventions, therefore reflecting the current routine care.

### Outcome measures

Outcome measures will be collected at baseline (t_0_), immediately post-intervention (t_1_), and six weeks after intervention (t_2_), by two trained research assistants (Master students of Nursing). To collect six-week follow-up outcome data, the researchers will reminder all the participants via text messages. The schedule of enrolment, interventions, and assessments of the trial is shown in Fig. 2, as recommended in the SPIRIT 2013 statement [35].

**Fig. 2 Fig2:**
[figure not shown]
Enrolment, interventions, and assessments of the trial (PSS: Perceived Stress Scale, BCS: Brief COPE Scale, ZBI: Zarit Burden Interview, NPI-Q: Neuropsychiatric Inventory-Questionnaire). *t*_*0*_: Baseline, *t*_*1*_: immediately post-intervention, *t*_*2*_: six weeks after the intervention

### Background characteristics

Sociodemographic characteristics of family members and their relative with dementia will be collected at baseline using a self-developed questionnaire. Data for family members include age (years), gender, ethnicity, educational attainment (primary school or lower, middle school, high school, or college/university), marital status (unmarried, married, divorced, or others), relationship with the resident (spouse, child, child-in-law, grandchild, or others), employment status (full-time, part-time, retired, or unemployed), whether lived with the resident before placement, and the proportion of facility fees that the family member or his/her family need to pay (almost zero, less than 20, 20 to 50%, 51 to 80%, or more than 80%). Data for residents with dementia include age (years), gender, ethnicity, educational attainment (primary school or lower, middle school, high school, or college/university), marital status (unmarried, married, divorced, or others), and length of stay in the studied facility (months).

In addition, for residents with dementia, disease-related data such as type of dementia (Alzheimer’s disease, vascular dementia, Lewy body disease, Parkinson’s disease, frontotemporal dementia, or others), time of diagnosis, and cognitive ability (e.g. Mini-Mental State Examination), will be extracted from the medical records.

### Stress

Family members’ stress will be measured using the 10-item Perceived Stress Scale (PSS-10), which was designed to tap how unpredictable, uncontrollable, and overloaded respondents find their lives during the last month [36, 37]. The questions in the PSS-10 adopt a five-point Likert scale ranging from 0 (never) to 4 (very often). The total score of the PSS-10 ranges from 0 to 40; a higher score suggests a higher level of stress. The Chinese version of PSS-10 has been validated, indicating a satisfactory internal consistency reliability for evaluating stress levels in Chinese population (Cronbach’s α = 0.86) [38].

### Coping strategies

Family members’ use of coping strategies will be measured using the 28-item Brief COPE Scale (BCS) [39]. This scale consists of 14 domains and adopts a four-point Likert scale ranging from 1 (I have not been doing this at all) to 4 (I have been doing this a lot). The total score of the BCS scale ranges from 0 to 112; higher scores indicate more frequent use of coping strategies. The Chinese version of the BCS has been validated, suggesting a satisfactory internal consistency reliability for evaluating use of coping strategies in Chinese population (Cronbach’s α = 0.79) [40].

### Caregiving burden

Family members’ caregiving burden will be measured using the 22-item Zarit Burden Interview (ZBI) [41]. This instrument covers family members’ health, psychological well-being, social life, finances, and relationship between the family members and their relative [41]. Each item of the ZBI is answered on a five-point scale (0 = never, 1 = rarely, 2 = sometimes, 3 = quite frequently, and 4 = always). The total score of the ZBI ranges from 0 to 88, with a higher score indicating a higher level of burden. The Chinese version of the ZBI shows a sound internal consistency reliability in Chinese family caregivers (Cronbach’s α = 0.875) [42].

### Family involvement

Family involvement will be assessed by several simple questions referring to Roberts, Ishler, & Adams [43]. The questions cover family visiting, providing personal care, and communicating with facility staff [44]. For visiting, families will be asked to estimate their average frequency of visiting the nursing home using these response options: daily, several times per week, once per week, two or three times per month, once per month, or a few times per year. They will be also asked how often they have helped their relative with dementia during visits in feeding, dressing, toileting, grooming, and going to activities on a scale of “never” (0), “sometimes” (1), or “always” (2). Responses to these five activities will be summed to indicate family involvement in providing personal care. For communication with facility staff, family members will be asked how often they have talked with four categories of facility staff members during the last month: care workers, nurses, physicians, and administrators on a scale of “never” (0), “sometimes” (1), and “always” (2). A measure of the overall level of communication with facility staff will be created as a sum of these responses. These questions have been translated into Chinese by the researchers for this study.

### BPSD

Residents’ severity of BPSD will be assessed by inquiring their primary nurse using the 12-item Neuropsychiatric Inventory-Questionnaire (NPI-Q) [45], which can also measure the impacts of BPSD to caregivers. Initial responses to each question are “yes” or “no”. If “yes”, the respondents will then be asked to rate the frequency and severity of the symptoms as well as the associated impacts. A higher score indicates a more severe BPSD and a higher level of caregiver distress. The Chinese version of the NPI-Q has been validated, suggesting a satisfactory reliability in Chinese residential care facility residents with dementia (Cronbach’s α = 0.64, intra-class correlation coefficient = 0.93) [46].

### Intervention fidelity and process evaluation

The fidelity of intervention implementation will be monitored and assessed. Prior to conducting the trial, an exhaustive protocol will be developed to guide implementation of the intervention. A checklist will be also developed for evaluating the intervention fidelity. The duration of each session and the attendance of the participants in each session will be recorded. Furthermore, outcome assessors will be trained to deliver the standardised assessment measures.

### Data management and analysis

Data will be double entered and checked in EpiData 3.1 (The EpiData Association, Odense, Denmark) and will then be exported to Statistical Package for the Social Sciences (SPSS) version 25.0 (IBM Corporation, Armonk, New York, USA) for analyses. The distribution normality of the continuous variables will be tested by One-Sample Kolmogorov-Smirnov test. The baseline homogeneity between the intervention group and the control group will be tested using the Student’s T test, Mann-Whitney U test, Chi-square test, and Fisher’s exact test, where appropriate. All outcome measures will be compared within and between groups. The generalised estimating equation (GEE) model will be utilised to analyse the intervention effects, with controlling for confounding factors such as the family members’ age, gender, educational attainment, and relationship with the residents, and the residents’ age, gender, educational attainment, type of dementia, and length of stay in the facility. The analyses will be performed based on the intention-to-treat (ITT) principle. For ITT analysis, missing data will be dealt by using the last observation carried forward method, whereby the last available measurement for each participant at the time point prior to withdrawal from the study is retained in the analysis [47]. Statistical significance will be set at *p* < 0.05; all tests will be two-tailed.

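### The GEE covariate list omits the outcome's baseline value and leaves the role of t0 unstated; adjusting for baseline would gain precision at no data cost

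*Protocol article*

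**What the plan says.** Under Data management and analysis, the protocol article gives the effectiveness model: "The generalised estimating equation (GEE) model will be utilised to analyse the intervention effects, with controlling for confounding factors". The examples begin "with controlling for confounding factors such as the family members’ age, gender, educational attainment, and relationship with the residents" and go on to five resident characteristics: age, gender, education, dementia type and length of stay. That makes nine. The outcome's own baseline score is not among them, and neither is the facility (length of stay is not a site term). The same section specifies intention-to-treat analysis with last observation carried forward (LOCF).

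Under Outcome measures: "Outcome measures will be collected at baseline", then immediately after the intervention (t1) and six weeks later (t2). Whether t0 is a repeated outcome in the GEE, a covariate, or unused is not stated.

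Under Sample size estimation: "Sample size is estimated based on the primary outcomes, specifically, changes in family members’ stress". Further, "effect size of family members’ stress reduction is anticipated to be medium at 0.50", and "a sample size of 128 participants (64 per group) will provide this study with 80% power at 5% level of significance (two-tailed"). The text does not say whether 0.50 is in SDs of the score or of the change, and it gives no correlation between baseline and follow-up.

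**The concern.** For a score such as the PSS-10, the baseline value is usually among the best predictors of the follow-up value. The plan names a set of adjusters for the treatment effect and leaves that one out, although it is already collected. Two models fit the text, and each leaves precision unused:

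- **t0, t1 and t2 as outcomes, with group-by-time terms.** The effect is a difference in mean change. Baseline is used, but with its coefficient fixed at 1 and not estimated.
- **t1 and t2 only as outcomes.** As listed, the model does not use the baseline score, and chance baseline imbalance stays in the estimate.

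What is at stake is the width of the confidence interval and the power at the planned size. Validity is not in question.

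**Working it through.** **1. The plan's own figure.** Inputs from Sample size estimation: effect 0.50, two-sided 5%, 80% power. By the noncentral t, power is 0.795 at 63 per arm and 0.801 at 64, so 64 per arm (128) reproduces. Attrition of 15%: 128/0.85 = 150.6, against the stated 150. No baseline adjustment is needed to reach these figures.

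**2. Variance factors.** Let the score have SD 1 at each visit, and let rho be the baseline-to-follow-up correlation. Rho is not given in the article, so 0.3 to 0.7 is assumed. The between-arm variance at one follow-up visit is proportional to:

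- follow-up only: 1
- change score: 2(1 − rho)
- baseline-adjusted: 1 − rho²

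Adjusted against change: (1 − rho²) / [2(1 − rho)] = (1 + rho)/2. Adjusted against follow-up only: 1 − rho², a saving of rho².

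| rho | change | adjusted | adjusted/change | saving v change | saving v follow-up only |
|---|---|---|---|---|---|
| 0.3 | 1.40 | 0.91 | 0.65 | 35% | 9% |
| 0.4 | 1.20 | 0.84 | 0.70 | 30% | 16% |
| 0.5 | 1.00 | 0.75 | 0.75 | 25% | 25% |
| 0.6 | 0.80 | 0.64 | 0.80 | 20% | 36% |
| 0.7 | 0.60 | 0.51 | 0.85 | 15% | 49% |

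At rho 0.7 the remaining variance is 0.51, so the saving against follow-up only is 1 − 0.51 = 0.49.

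**3. Power at 64 per arm (noncentral t).** The answer depends on the SD that 0.50 refers to, so both scalings are shown.

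- *0.50 in SDs of change.* The change contrast has 80% power at every rho. After adjustment the standardised effect is 0.50/√[(1+rho)/2], and power is 94%, 92%, 90%, 88% and 86% for rho 0.3, 0.4, 0.5, 0.6 and 0.7.
- *0.50 in SDs of the score.* Change contrast against adjusted: 66% v 84%, 73% v 86%, 80% v 90%, 88% v 94% and 95% v 98% for the same rho values. Follow-up only has 80% throughout.

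**4. Simulation check.** Simulated trials with 64 per arm, three visits and an exchangeable GEE (600 runs per rho) gave these variance factors at rho 0.3, 0.5 and 0.7:

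- group-by-time GEE: 1.41, 1.09, 0.64
- baseline-adjusted model: 0.85, 0.83, 0.55
- GEE with a common baseline mean: 0.85, 0.82, 0.55

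These agree with step 2 within simulation error. The last two models are practically the same.

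**5. What the listed covariates do.** LOCF gives every participant with a baseline a value at all three visits. In such balanced data, a main effect of a characteristic that is constant over time does not touch the group-by-time contrast. One simulated data set (150 participants, three visits, about 15% carried forward, exchangeable GEE) gave the same arm-by-time estimates and robust standard errors to 8 decimals with and without nine such covariates. Under that model the named adjusters cannot stand in for baseline adjustment. A facility main effect would not move the contrast either.

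**The case against.** The strongest reply is that the list is illustrative, since it opens with "such as", and that a condensed article may leave the handling of t0 to the full protocol or analysis plan. Powering on change suggests that baseline is used somehow. This stands in part: it cannot be said that the trial will ignore baseline, only that the article does not name it and does not say how t0 enters. The suggestion survives because baseline adjustment gains precision under either model compatible with the text.

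A reader might also infer any of the following, which the document does not support:

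- **The estimate is biased.** It is not shown to be. Under individual randomisation, both a change contrast and a follow-up comparison are unbiased.
- **The sample size is wrong.** The 128 reproduces without baseline adjustment.
- **A quarter of the precision is lost.** That figure holds only at rho 0.5, an assumed value.
- **The nine covariates both do nothing and destabilise the model.** These belong to different models. They leave a group-by-time contrast unchanged, so they cannot destabilise it. In a model of t1 and t2 only, they may do some good. Under LOCF the analysed number is also nearer 150 than 128. Shortening the list is a matter of preference.
- **Leaving out facility is a serious fault.** No stratification by facility is described and no intraclass correlation is given. It is a small precision matter that cannot be quantified.

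**Conclusion.** The point holds as one of efficiency and unclear specification. Against a group-by-time contrast, baseline adjustment would cut the variance by 35% to 15% for rho 0.3 to 0.7. Against a model of t1 and t2 without baseline, it would cut it by 9% to 49%. The rise in power from 80% to between 94% and 86% assumes that 0.50 is in SDs of change; on the score scale the gain ranges from 18 points (rho 0.3) to about 2 points (rho 0.7). All these figures rest on an assumed rho and on equal variances across visits. The formulas are for fully observed data, and values carried forward would change the effective correlation somewhat. The facility term carries no figure.

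**What to change.** In Data management and analysis, state the model for each outcome: t1 and t2 as repeated outcomes, with arm, time, arm-by-time and the baseline value of that outcome. Equivalently, keep t0, t1 and t2 as outcomes and fit one common mean at t0 for both arms. In the t1/t2 model, add facility as a fixed effect for precision; with four to six sites this takes three to five degrees of freedom. The other listed covariates may stay. The cost is analysis wording only: baseline scores are already planned at t0, and each participant is recruited through a known facility. The sample size need not change.
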